### Intervention

Every 2 weeks, the parents or caregivers of test group will receive educational mobile messages related to the prevention of ECC via WhatsApp Messenger. These materials will be developed by the researchers from the insights, including main doubts, questions, and challenges, regarding the disease, collected from the focus groups, conducted previously with the participation of a sample of parents or caregivers who attended the Clinics of Bauru School of Dentistry. These text messages will be formulated with a simple language for a better understanding, which will include emoticons and short and direct videos. The participants will be instructed to activate the function *read receipts* to confirm their adherence and engagement with the study. The participants’ feedbacks related to the quality and utility of electronic messages for ECC prevention will be collected only after the 12-month follow-up, to avoid blinding biases.

All dyads of parents and children will be invited for dental appointments on a quarterly basis. The children will be examined by a trained and calibrated dental professional for the measurement of primary outcomes, receiving a subsequent dental prophylaxis. When necessary, fluoride varnish (Duraphat, Colgate) will be applied on dental demineralized surfaces (ICDAS=1 or 2), whereas a conventional glass ionomer cement (Ketac Molar Easymix, 3M) will be used for sealing localized enamel lesions (ICDAS=3). The investigators will not be informed about the origin of groups of participants, characterizing a single-blind study.

### Sugar Consumption

A questionnaire developed by Llena and Forner [26] to investigate the dietary habits of dental patients will be applied at baseline and after the 12-month follow-up to evaluate the influence of sugar consumption on the development of oral diseases. The different types of food are divided into 9 categories: (1) foods containing sticky sugars: dried fruit, candies containing sugar, jellies, jams, and sauces; (2) foods containing starch and sugar: cookies, cereals, and industrialized cakes; (3) candy without sugars; (4) milk and dairy products containing sugar: chocolate, yogurt, creams, ice creams, and flans; (5) milk and dairy products without sugar: pure milk, sugar-free yogurt, and cheese; (6) sugary beverages: juices and soft drinks; (7) fruits: fruits and juices; (8) semihydrolyzed starch-rich foods: potato chips, French fries, industrialized bread, and rolls; and (9) sugar-free foods: nuts, bread, pasta, and noodles.

### Study Outcome Measures

The primary outcomes will be related to the oral health status of children and the risk factors for ECC. For that, ICDAS, VPI, and CPITN indices will be determined for the recruitment of participants at baseline and 3-, 6-, 9-, and 12-month follow-ups.

The secondary outcomes will be related to the measurement of the influence of educative strategies on parents or caregivers, considering their patterns of sugar consumption, their level of eHealth literacy, and their individual perceptions about their own ability in executing specific activities. These data will be collected at baseline and after the 12-month follow-up using the questionnaire for sugar consumption [26], the instruments eHEALS [23], and General Perceived Self-Efficacy Scale (GSES) [27], respectively. In addition, the results of eHEALS will be applied for the recruitment of participants.

GSES measures the individual’s beliefs about their cognitive, motivational, behavioral, and affective skills needed to perform particular tasks. It comprises 10 questions with answers arranged in a 4-point Likert scale, with options ranging from *not at all true* through *exactly true*. The total score ranges between 10 and 40 points, with greater scores indicating higher overall perceived self-efficacy of individuals [27].

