**Methods:**

A single-blinded, randomized, and parallel-group clinical trial will be conducted with dyads of parents or caregivers and children aged between 36 and 60 months, recruited from kindergartens and schools of Bauru, São Paulo. The determination of sample size resulted in a total of 104 dyads of parents and children, considering a power of 80%, a significance level of 5%, and an attrition of 30%. This sample will be randomly assigned to test and control groups, being divided in 52 dyads per group according to the health literacy levels of parents and the age, gender, and oral health status of children. Every 2 weeks, only participants in the test group will receive messages via WhatsApp containing preventive and education-related ECC information. The dyads will visit the dentist every 3 months during a year for the assessment of primary outcomes (sugar consumption and the International Caries Detection and Assessment System, visible plaque, and community periodontal indices) and to receive dental care measures. Secondary outcomes (electronic health literacy and general perceived self-efficacy) will be determined only at baseline and after 12-month follow-up. The quality of randomization will be evaluated throughout the study, comparing the test and control groups systematically by Student t tests for continuous variables and chi-square tests for categorical variables. Listwise deletion method will be applied in cases of dropouts, if the missing values satisfy the criteria of missing completely at random; otherwise, multiple imputation data strategy will be conducted. The Kolmogorov-Smirnov and Levene tests will be used to determine the normality and homogeneity of data, respectively, which will indicate further statistical analyses for elucidating significant differences between groups (P<.05). A Student t test or Mann-Whitney U test will be employed for parametric or nonparametric analyses, respectively.

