### Objectives

Therefore, new approaches are required to prevent ECC, aiming to improve the awareness about its consequences for deciduous and permanent dentitions, in addition to promoting the engagement of parents or caregivers with healthy behaviors toward the maintenance of oral health status of their children. In this sense, this study aims to assess the effectiveness of educational mobile messages sent via WhatsApp Messenger as an adjuvant method for the prevention of ECC in children of a given population. The null hypotheses for this study indicate that the educational mobile messages will not be effective for aiding in the control of dental plaque (H_0_), the decrease of sugar consumption (H_0_′), the maintenance of the International Caries Detection and Assessment System (ICDAS) indices (H_0_′′), and the improvement of parents’ electronic health (eHealth) literacy levels (H_0_′′′) after 12-month follow-up.

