### Data Analysis

Statistical analysis will be performed using SPSS Statistics software 21.0 (IBM SPSS Statistics). The data will be presented with descriptive statistics, being examined for lost values, outliers, normality, and homogeneity. To investigate the quality of randomization, potential differences between the characteristics of participants of the test and control groups will be determined systematically, applying Student *t* tests for continuous variables and chi-square test for categorical variables. Listwise deletion method will be adopted in cases of dropouts, if the lost values satisfy the criteria of the missing data completely at random; otherwise, multiple imputation data strategy will be used. The Kolmogorov-Smirnov and Levene tests will be used to analyze the normality and homogeneity of data, determining further statistical tests for detecting differences between groups (*P*<.05). A Student *t* test or Mann-Whitney *U* test will be employed for parametric or nonparametric analyses, respectively.

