## Results

At this moment, 104 dyads have already been recruited. The parents or caregivers have responded the questionnaires, while children are being examined to determine their baseline oral health status. From August, 2019, dyads will be allocated to control or test groups. The parents or caregivers will receive the first electronic message after 15 days of allocation. The first results related to oral health status of children are expected to be obtained in November, 2019. The data collection will be performed during 12 months, between August 2019 and 2020.

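### The primary outcomes differ between sections, do not match the null hypotheses, and carry only a P<.05 threshold with no stated control of error across them

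*Protocol article*

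**What the plan says.** Four places in the protocol article define what the trial is meant to show.

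- **Abstract, Methods.** Four outcomes are primary and are assessed at the three-monthly visits: "primary outcomes (sugar consumption and the International Caries Detection and Assessment System, visible plaque, and community periodontal indices". Only eHealth literacy and self-efficacy are secondary.
- **Study Outcome Measures.** Three outcomes are primary: "ICDAS, VPI, and CPITN indices will be determined for the recruitment of participants at baseline and 3-, 6-, 9-, and 12-month follow-ups". Sugar is listed among the secondary outcomes, which are described as "considering their patterns of sugar consumption, their level of eHealth literacy, and their individual perceptions about their own ability in executing specific activities". Collection of the latter is at baseline and 12 months only. The Sugar Consumption section gives the same two time points.
- **Objectives.** There are four separately labelled null hypotheses, set after 12 months of follow-up. The first is that the messages "will not be effective for aiding in the control of dental plaque". The others concern sugar consumption, ICDAS and eHealth literacy.
- **Data Analysis.** Normality and homogeneity checks come first, "determining further statistical tests for detecting differences between groups" at P<.05. Then: "A Student *t* test or Mann-Whitney *U* test will be employed for parametric or nonparametric analyses, respectively". No outcome, time point or adjustment is attached to that threshold.

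The Sample Size section gives 104 dyads for 80% power, 5% significance and 30% attrition. It refers to the outcomes of a cited study and does not name the outcome used.

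**The concern.** A confirmatory trial needs to say in advance which result will count as showing that the intervention works. Here the three places that should say so disagree, and none names a single endpoint. A favourable result on plaque alone, caries alone, gingival status alone or sugar alone could each be presented as the primary finding, with some section of the protocol in support.

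Two things are at stake. First, the headline claim can be settled after the data are seen. Second, if one success among several is enough, the 5% significance level in the sample size section no longer describes the risk of a false claim.

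**Working it through.** **1. The lists side by side**

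| Outcome | Abstract | Study Outcome Measures | Null hypothesis at 12 months |
|---|---|---|---|
| ICDAS | primary | primary | yes |
| VPI (plaque) | primary | primary | yes |
| CPITN | primary | primary | none |
| Sugar consumption | primary | secondary | yes |
| eHealth literacy | secondary | secondary | yes |
| Self-efficacy | secondary | secondary | none |

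Only ICDAS and VPI are primary in both lists and also have a hypothesis. The abstract also places sugar among outcomes assessed every three months, while the main text measures it only at baseline and 12 months.

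**2. The plan's own figure**

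The protocol states no familywise error rate, so there is none to reproduce. The 104 dyads (52 per arm) cannot be re-derived, because no outcome, effect size or SD is given. The figure fits 36/(1 − 0.30) = 51.4, rounded up to 52 per arm. It also fits 40 × 1.30 = 52 per arm. It is not shown to be wrong, but it does not reveal which outcome was powered.

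**3. Chance of at least one false positive at 12 months**

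Assumptions: two-sided 0.05 per test (sidedness is not stated), no true effect on any outcome, and any one significant result counts as effectiveness.

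For k independent tests the chance is 1 − 0.95^k.

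- k = 3: 1 − 0.95^3 = 14.3%
- k = 4 (the abstract's primaries, or the four stated hypotheses): 1 − 0.95^4 = 18.5%

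The correlation between outcomes is not given. Multivariate-normal simulation (300,000 draws) over an assumed range gives:

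| Between-outcome correlation | 3 outcomes | 4 outcomes |
|---|---|---|
| 0 | 14.2% | 18.6% |
| 0.3 | 13.5% | 17.2% |
| 0.5 | 12.6% | 15.5% |
| 0.7 | 11.0% | 13.0% |

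The ranges are therefore about 11–14% for three outcomes and 13–19% for four.

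**4. The same, if every visit were also tested (hypothetical)**

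Three indices at four visits make 12 tests: 1 − 0.95^12 = 46.0% if independent. Adding sugar at 12 months makes 13: 1 − 0.95^13 = 48.7%. Simulated ranges cover between-outcome correlation 0.5 down to 0, with sugar treated as independent of the rest:

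| Between-visit correlation | 12 tests | 13 tests |
|---|---|---|
| 0 | 41.4–46.0% | 44.5–48.6% |
| 0.5 | 35.6–39.8% | 38.8–42.9% |
| 0.7 | 30.3–34.2% | 33.7–37.5% |
| 0.9 | 22.5–25.5% | 26.3–29.1% |

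The overall span is about 23–49%.

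**5. Price of keeping several primaries**

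Assume 36 evaluable per arm and an effect with 80% power at 0.05: d = (1.960 + 0.842) × √(2/36) ≈ 0.66. At the Bonferroni level for three outcomes, 0.05/3 = 0.0167, the critical value is 2.394. Power is Φ(2.802 − 2.394) ≈ 66%. For four, at 0.0125, it is about 62%. Restoring 80% at those levels would need about 1.33 and 1.42 times the sample.

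**The case against.** **The hypotheses may stand separately.** Objectives labels four hypotheses on distinct constructs. If each supports only its own conclusion, each has its own 5% error and familywise control is debatable. The 5% in Sample Size is an input to a calculation, not a promised familywise rate. This stands as far as it goes: the figures above depend on an any-one-is-enough rule, which the documents neither state nor exclude. It does not explain why CPITN is primary with no hypothesis, or why sugar changes rank between sections.

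**A multiplicity rule may sit in an analysis plan that is not shown.** That is possible, and the lack of an adjustment method would not be a finding on its own. But choosing the primary endpoint and keeping the sections consistent belong to the protocol. An analysis plan cannot adjust across a primary family that the protocol defines in conflicting ways.

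**A stronger reading is tempting.** A reader might infer from the four follow-up visits that twelve tests are planned, so that the trial would claim effectiveness by chance a third to a half of the time. The documents do not support this. They say that the indices are measured at each visit, not that the groups are compared at each visit, and the hypotheses are tied to 12 months. The Results statement, "The first results related to oral health status of children are expected to be obtained in November, 2019", fits the first follow-up examinations and announces no between-group test. Even if every visit were tested, a third to a half needs a between-visit correlation of at most about 0.7.

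**Conclusion.** The concern holds in this form: the primary outcome set is inconsistent between the abstract and the main text, the null hypotheses match neither list, and the only stated decision rule is an unadjusted P<.05. The confirmatory claim is undefined as written. This part rests on the text alone and needs no assumption.

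The size of the error is conditional. If any one significant primary result is read as effectiveness, the false-claim rate at 12 months is about 11–14% with three outcomes and 13–19% with four, two to almost four times the nominal 5%. The 23–49% range applies only if every visit is tested as well, and should be quoted only as a hypothetical. All correlations are assumed.

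The documents do not show which outcome should be the primary. Plaque has the first-listed hypothesis, but list order does not establish primacy, and the stated aim of preventing caries points at least as readily to ICDAS.

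**What to change.** Before any follow-up data are seen:

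1. Name one primary endpoint at 12 months, namely the outcome on which the 104-dyad sample size was based, and state that basis in Sample Size. Test the other outcomes as secondary.
2. Alternatively, if several primaries are kept, apply Holm at two-sided 5% across the 12-month primary tests.
3. Report the 3-, 6- and 9-month comparisons as supportive estimates with confidence intervals, with no claim of effectiveness resting on them.
4. Make the abstract, Objectives and Study Outcome Measures give the same primary outcomes, secondary outcomes and hypotheses. In particular, settle the rank of sugar consumption, the missing CPITN hypothesis and the status of the eHealth literacy hypothesis.

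The cost is mainly wording in the protocol and analysis plan, and an update of the registration where it differs. The Results section has allocation starting in August 2019 with baseline examinations still under way, so at that stage the change could precede all follow-up.

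With one primary endpoint, 104 dyads needs no change for multiplicity, but fewer outcomes can carry a confirmatory claim. With three primaries, per-test power is about 66% rather than 80% at the Bonferroni level, under the assumptions in step 5 of the working. That level is Holm's first step, so Holm's power per test is no lower.

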### Data Analysis

Statistical analysis will be performed using SPSS Statistics software 21.0 (IBM SPSS Statistics). The data will be presented with descriptive statistics, being examined for lost values, outliers, normality, and homogeneity. To investigate the quality of randomization, potential differences between the characteristics of participants of the test and control groups will be determined systematically, applying Student *t* tests for continuous variables and chi-square test for categorical variables. Listwise deletion method will be adopted in cases of dropouts, if the lost values satisfy the criteria of the missing data completely at random; otherwise, multiple imputation data strategy will be used. The Kolmogorov-Smirnov and Levene tests will be used to analyze the normality and homogeneity of data, determining further statistical tests for detecting differences between groups (*P*<.05). A Student *t* test or Mann-Whitney *U* test will be employed for parametric or nonparametric analyses, respectively.

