### Sample Size

The calculation of this sample size was performed using the Open Source Epidemiologic Statistics for Public Health, following the criteria and outcomes described by Zotti et al [25]. It resulted in a total of 104 dyads of parents and children, considering a power of 80%, a significance level of 5%, and an attrition of 30%.

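### Dropouts are deleted or imputed according to a check of missing completely at random (MCAR) that cannot establish MCAR; if loss differs by arm, the completers' comparison can be biased

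*Protocol article*

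**What the plan says.** The Data Analysis section sets a two-branch rule. The first branch is "Listwise deletion method will be adopted in cases of dropouts, if the lost values satisfy the criteria of the missing data completely at random". The second is "otherwise, multiple imputation data strategy will be used". The abstract (Methods) repeats the rule: "Listwise deletion method will be applied in cases of dropouts, if the missing values satisfy the criteria of missing completely at random". Neither place names a test, variable or threshold for MCAR. Groups are then compared by a Student t or Mann-Whitney U test, and the section names no covariate adjustment.

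On size, the Sample Size section says: "It resulted in a total of 104 dyads of parents and children", with 30% attrition allowed for. The abstract gives the split: "being divided in 52 dyads per group".

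Three other sections bear on who may be lost:
- Intervention: only the test arm gets messages every two weeks. Both arms are invited to quarterly appointments.
- Study Outcome Measures: the clinical indices (ICDAS, VPI, CPITN) are taken at baseline and at 3, 6, 9 and 12 months.
- Discussion: low caregiver health literacy is linked both to poorer child health and to fewer medical visits.

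**The concern.** The set of dyads in the main comparison depends on a preliminary check that cannot deliver what the rule asks of it. MCAR is a statement about unseen values as well as seen ones. Observed data can contradict it but never confirm it, at any sample size. In practice the rule becomes: delete unless the check is significant.

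The protocol itself gives reasons to doubt MCAR. Its Discussion ties one caregiver characteristic to both child health and attendance. The fortnightly messages are an extra contact in one arm only, so the kind of family lost may differ by arm. If it does, deleting dropouts and comparing the remainder without adjustment no longer preserves the randomised comparison.

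Deletion also gains nothing in bias. Where MCAR holds, correctly specified multiple imputation is valid too. Where loss depends only on observed values, imputation that includes them remains valid, while the unadjusted completers' comparison may not.

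**Working it through.** **The plan's own figure.** The total of 104 cannot be rebuilt, because the article gives no effect size or SD. The attrition step fits 36 per arm (36 / 0.7 = 51.4, rounded up to 52) and equally 40 per arm (40 × 1.3 = 52). The point does not depend on which was used.

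**Dyads at stake.** 0.30 × 104 = 31.2, so about 31 dropouts and 73 completers at planned attrition.

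**Power of a baseline check.** For a standardised mean difference d between dropouts and completers, two-sided 5%, normal approximation:

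- SE = √(1/31 + 1/73) = 0.214
- Power = Φ(d / SE − 1.96)

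| d | d / SE | Power |
|---|---|---|
| 0.2 | 0.93 | 15% |
| 0.3 | 1.40 | 29% |
| 0.4 | 1.87 | 46% |
| 0.5 | 2.33 | 65% |
| 0.6 | 2.80 | 80% |

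**Consequence of following the rule.** This was simulated with 4,000 trials per setting. From the protocol: 52 per arm, 30% loss, an unadjusted t test on completers. Assumed: no true effect, baseline-outcome correlation 0.6, dropout depending on baseline in controls only, and MCAR taken as satisfied when a t test of baseline between dropouts and completers gives P ≥ .05. Bias and type I error are among the trials that pass the check.

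| Odds ratio of dropout per SD (controls only) | Check passed | Bias (SD) | Type I error |
|---|---|---|---|
| 1.5 | 85% | 0.07 | 6.0% |
| 2.0 | 69% | 0.11 | 8.6% |
| 2.5 | 56% | 0.15 | 9.8% |

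Repeat runs agree closely on pass rate and bias. Type I error at odds ratio 2 varied between about 6% and 9%. With 52 × 0.7 = 36.4 completers per arm, the standard error of the difference is √(2 / 36.4) = 0.23 SD, so the bias is about 0.3 to 0.7 of a standard error. Its direction depends on which children are lost from which arm.

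**Where the harm vanishes.** With the same baseline-related dropout in both arms, bias is about zero. The check then passes in about 55%, 14% and 3% of trials at odds ratios 1.5, 2 and 2.5, so at the stronger settings most trials go to imputation. In the control-only setting, deleting the same dropouts but adjusting for baseline also gives bias of about zero. The harm therefore comes from deletion combined with an unadjusted test, under loss that differs by arm.

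**The case against.** The strongest reply has four parts.

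1. **Multiple imputation is in the same sentence of the plan.** True, and a reader should not infer that dropouts are always deleted. But imputation applies only when the check rejects, and a weak check often will not.

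2. **The simulated check is not the protocol's.** This stands. The protocol names no check, so the pass rates describe one plausible device under assumed mechanisms. Leaving the choice of test to a fuller document is acceptable. The objection here is to letting any such test choose the analysis, and the article states that rule outright.

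3. **The bias comes from the missing adjustment, not from deletion.** This stands in part: adjusting for baseline removes it in the simulated setting. The Discussion does promise to take sociodemographic confounders into account, but the Data Analysis section names only two-group tests.

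4. **Larger biases can be produced, but not fairly charged to this rule.** When dropout depends on the unseen outcome in opposite directions by arm, bias of 0.28 to 0.54 SD can be generated. Multiple imputation would not correct that either, so those figures are not used here.

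Three stronger readings are also tempting and lack support:
- A reader might infer that controls have no contact at all. The Intervention section gives both arms quarterly appointments, and only the messages differ.
- A reader might infer that a child who misses any one visit is removed, which would cut the complete records sharply. The rule speaks of dropouts, the planned tests compare two groups, and the Objectives set the hypotheses at 12 months. No complete five-visit record is required.
- A reader might take 30% as the most that could be excluded. It is a planning allowance, not a ceiling.

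**Conclusion.** The concern holds in a conditional form. The rule lets a check that cannot establish MCAR, and has low power against moderate departures with about 31 dropouts and 73 completers, decide whether roughly 30% of the randomised dyads are left out. If loss depends on prognosis differently by arm, the unadjusted completers' comparison is biased. Under the assumptions tabulated above the effect is modest, at most about 0.15 SD of bias and a type I error of about 10%. The odds ratios, the correlation and the form of the check are assumptions, not figures from the protocol.

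A reader might conclude that the trial's result will be biased. The documents do not support that: bias is about zero under true MCAR or similar loss in both arms, and nothing in the article shows that loss will differ. This is a should-fix point, because a better method is already in the plan, and not a must-fix one.

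**What to change.** In the Data Analysis section and the abstract, delete the condition on MCAR and state instead:

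- The primary analysis includes all randomised dyads in their allocated arm.
- Missing outcomes are multiply imputed within arm, with the baseline value of the outcome, the stratification factors and any earlier observed visits in the imputation model. For outcomes collected only at baseline and 12 months there are no intermediate visits to use.
- The comparison between arms is adjusted for the baseline value.
- Listwise deletion is kept as a sensitivity analysis only.

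The cost is revised wording and a little more analysis work, since multiple imputation is already planned as the alternative branch. There is no change to sample size, visits or data collected. According to the Results section, allocation was to begin in August 2019 and data collection to run to August 2020, so on that timetable the rule could be settled before the 12-month outcomes were known. One limitation remains: imputation does not correct loss that depends on outcomes nobody observed, and the report should say so.

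### Multiple imputation is paired with a pretest-selected t or Mann-Whitney test; on the Mann-Whitney branch the plan as written gives one P value per imputed data set and no single result

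*Protocol article*

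**What the plan says.** The Data Analysis section of the protocol article fixes two rules.

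- **Missing data.** The first branch reads "Listwise deletion method will be adopted in cases of dropouts, if the lost values satisfy the criteria of the missing data completely at random". For every other case the section turns to imputation: "otherwise, multiple imputation data strategy will be used". The trigger for imputation is any departure from missing completely at random (MCAR), which includes missing at random (MAR).
- **Choice of test.** "The Kolmogorov-Smirnov and Levene tests will be used to analyze the normality and homogeneity of data", with the results "determining further statistical tests for detecting differences between groups". The two candidates are Student t and Mann-Whitney U, of which each "test will be employed for parametric or nonparametric analyses, respectively".

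The abstract repeats both rules and closes with the same pair of tests: "A Student t test or Mann-Whitney U test will be employed for parametric or nonparametric analyses, respectively". No other between-group test of the outcomes is named.

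The Sample Size section allows for substantial loss: "It resulted in a total of 104 dyads of parents and children, considering a power of 80%, a significance level of 5%, and an attrition"; the attrition figure there is 30%. The abstract gives the split, "being divided in 52 dyads per group". Under Eligibility Criteria the clinical indices are discrete and bounded: visible plaque is read on six teeth, the periodontal index is scored 0, 1 or 2, and ICDAS is at most 3 at entry.

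**The concern.** Each rule is usable alone. Together they leave a gap on one branch. Multiple imputation gives m completed data sets, and the inference comes from combining an estimate and its variance across them. The t branch supplies a mean difference with a standard error, so it can be pooled. The Mann-Whitney branch, as the plan describes it, supplies a rank statistic and a P value, and Rubin's rules do not apply to P values directly.

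If the MCAR check fails and an index is judged non-normal, the analyst following the text holds m P values with nothing to say which one, or which function of them, answers the trial's question. At stake is the type I error of the between-group comparison. Several obvious shortcuts leave out the uncertainty due to the missing values, and others do not, so the conclusion can turn on an unstated choice.

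**Working it through.** **Inputs from the article.** 104 dyads, 52 per arm, 5% significance, 80% power, 30% attrition. At 30% loss about 0.30 × 52 = 15.6, or 16 values per arm, would be imputed.

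**The plan's own figure.** 104 cannot be derived from first principles, because the effect size and SD come from a cited study. It fits two routes: 36 / 0.70 = 51.4, rounded up to 52 per arm, or 40 × 1.30 = 52 per arm. With d = (1.96 + 0.84) × √(2/n), these imply d = 0.66 (n = 36) or 0.63 (n = 40). Nothing below depends on which was used.

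**What pooling requires.** For an estimate Q_j with variance V_j in completed set j = 1…m:

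- pooled estimate = mean of Q_j
- W = mean of V_j; B = sample variance of Q_j
- total variance T = W + (1 + 1/m) × B

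A P value has no V_j, so T cannot be formed from P values. The Mann-Whitney statistic can be re-expressed as the probability index U / (n1 × n2), which has a standard error and so can be pooled. Testing one completed set uses W alone and drops B.

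**Simulation under no effect.** Four null simulations, 52 per arm, scores from 0 to 6, imputation model including arm. All distributions, correlations and dropout models are assumptions, not figures from the article.

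- A: five visits, binomial-of-6 plaque score, latent correlation 0.6, about 29% MAR dropout depending on the last plaque score; m = 5 (2500 trials) or 20 (1200 trials).
- B: skewed score, correlation 0.5 with baseline (one run at 0.2), 30% MAR dropout depending on baseline and arm; predictive mean matching or Bayesian regression; m = 5 or 20; 3000 trials per setting (1500 for the run at 0.2). The Monte Carlo error for 3000 trials is √(0.05 × 0.95 / 3000) = 0.4 points.
- C: baseline and one follow-up, correlation 0.6, 29% MAR dropout, m = 5, 2500 trials.
- D: roughly 25 to 30% MAR dropout, m = 5.

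Type I error in %, nominal 5% (a dash means no figure):

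| How the sets are used | A | B | C | D |
|---|---|---|---|---|
| One completed set, Mann-Whitney | 13 | 11.2–12.9 | 11.0 | 11 |
| Median of the P values | 9–10 | 7.9–9.3 | 7.5 | 9 |
| Mean of the P values | – | 4.3–5.5 | 4.9 | – |
| Probability index, Rubin-pooled | 5.0–5.3 | 4.3–4.5 | – | 5 |
| Mean difference, Rubin-pooled | – | 3.5–5.0 | – | 5 |
| Complete cases, Mann-Whitney | 4.5–5.2 | 4.2–5.5 | – | – |

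Cruder shortcuts in B were far worse at m = 5: 27 to 30% if any significant set counts, and 45 to 46% if the sets are stacked as one. With less dropout (B, m = 5) the single-set figure falls to 9.0% at 20% and 7.0% at 10%.

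**Is the rank test the cause?** In C the t test was run alongside. One completed set: t 11.0%, Mann-Whitney 11.0%. Median P: t 7.8%, Mann-Whitney 7.5%. P values on both sides of .05 across sets: t 21.6%, Mann-Whitney 22.0% of trials. The two tests behave alike, so the inflation comes from not pooling.

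**The case against.** The strongest reply is that the pooling rule, the number of imputations and the imputation model are normally left to a statistical analysis plan, which is not shown, and that the article states no wrong pooling rule. That stands for the imputation details, and their absence is not the point. What remains is that the article does fix the pair of methods, and an analysis plan that followed it literally would still have to add an estimate with a standard error.

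It is also fair that the inflated error rates belong to procedures the article never proposes. They show what follows if the gap is filled badly.

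Several stronger readings are tempting, and the documents do not support them:

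- *The two methods cannot be combined at all.* They can. The pooled probability index held its level, as did pooled Mann-Whitney z-statistics (4.2 to 4.7% in B at 30% dropout).
- *Every shortcut inflates the error.* The mean P did so little or not at all.
- *Imputing is worse than not imputing.* Complete cases held their level in these null scenarios, but no scenario was run in which complete-case analysis is biased, which is the situation imputation is meant for.
- *This is the expected path.* It needs both a failed MCAR check and a non-normal verdict. The 30% is a sample-size allowance, not a forecast of mechanism, and how the indices become one score per child is not given. Foreseeable is as far as the text goes.
- *The pretests will select different tests in different imputed sets.* The article never says they are rerun in each set. In A, Kolmogorov-Smirnov verdicts differed between sets in 55 to 83% of trials with the asymptotic version but under 1% with the Lilliefors correction, and the article does not say which version applies.

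**Conclusion.** The point holds in a limited form. On the branch where dropout is not MCAR and the data are judged non-normal, the abstract and the Data Analysis section together define no single result. If the gap is filled without proper pooling, type I error at a nominal 5% rises to about 11 to 13% for one completed set and about 8 to 10% for the median P. It stays near 4 to 6% for the mean P and near 4 to 5% for a Rubin-pooled probability index or mean difference.

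The sizes rest on assumed 0–6 score distributions, correlations and MAR dropout of about 25 to 30%. One completed set and the median P exceeded 5% in every null setting run, including 10% dropout (7.0% and 6.3%). This is a gap worth closing before analysis. It does not show that the trial's comparison is invalid.

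**What to change.** In the abstract's Methods and in Data Analysis, state that where data are imputed:

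- one pre-specified analysis that returns an estimate and a standard error is applied to every completed data set, for example a linear or ordinal model with arm, baseline value and the stratification factors, or the Mann-Whitney probability index with its standard error;
- results are pooled by Rubin's rules and reported as one estimate with a 95% CI;
- no normality or variance check selects a test within imputed sets.

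The cost is a few sentences and slightly more programming, with no new data or participants. The pooled analysis will reject less often than the shortcuts: in one run of B with a true effect (30% dropout, m = 5) the pooled index rejected in 61.7% of trials, against 71.0% for a single completed set and 61.8% for complete cases. The gap to the single set is not power lost, because the single-set test does not hold its 5% level.
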